**3.7.2.2. Phase 2: Evaluation of Effectiveness of Community Intervention (Intervention description)**

Participants in the intervention arm will receive community based educational intervention. Each of them will be required to follow the educational intervention which will be given every 15 days for 3 months and should register their names and phone numbers (even family phone numbers) for tracking and reminding purpose. To do this, we, research team, will take the following points into consideration: first, building rapport (good interaction); second, facilitating supportive environment including social and psychological environment; third, motivation of participants to use the screening services and encouraging the positive act. Finally, women centered empowerment words and languages to maintain the health issue to be sustained in the groups. This makes not to be snap shot action for the participants to value their health in future endeavors. All of the participants will be promised of the confidentiality throughout the process.

**3.7. 2.3. Control group**

The control group will receive usual services from health extension workers. These participants will only receive a welcome message at the beginning, to validate their entry into the study, and a message at the end of the follow up to thank them for their participation. These participants will not receive specially prepared community based educational intervention.

**3.7.2.4. Participant follow-up**

All of the participants in control and intervention arms will attend the three visits, one at baseline after three months, and the other at the end (after six months).

**3.7.2.5. Intervention**

Educational intervention will be prepared based on health belief model constructs and distal factors which are interlinked with breast screening behavior. In addition, the intervention will be emerged from qualitative parts will be treated as distal factors in the model and used as very important base for intervention designing. Educational intervention will be provided on mammography, breast self-examination and breast clinical exam by training and teaching using different methods and materials like posters and brochures.

**3.7.3. Data Collectors**

In both phases, health professionals who hold B.Sc. degree and above will be recruited for data collection of qualitative, baseline, after three months and end of intervention (after six months). In case of qualitative, principal investigator act as data collector together with other data collectors. The same sex moderator will be used to reduce sensitivity. Supervisors who hold B.Sc. degree and above will also be assigned for supervision.

## Data Quality Control

As it has been explained above in the sampling part, districts (woredas/city administrations) for control and interventional groups will be selected randomly while considering the optimum distance between control and intervention group to prevent information contamination and to distribute socioeconomic variables difference between districts. The instrument designed based on literature review will be approved for validity and reliability. Community based intervention based on health belief model constructs will be designed by the research team who are in the field health education and promotion and applied thoroughly by trained health professionals. Data collection will be supervised and checked before electronic data entry by principal investigator and other study team member closely supervise to assure the maximum quality level. Then, double data entry verification method will be employed in separated spread sheet and data accessibility will be restricted to data manager and study principal investigator. Before analysis, data will be checked for normality and homogeneity, then analyzed & interpreted by research team and biostatistician. Finally, quality scientific report will be developed and disseminated.

## Data Analysis

Qualitative data will be analyzed by Atlas ti.7 software and use narration and direct quotation. For quantitative, analysis at baseline**, e**quivalence of two arms will be analyzed at baseline. The equivalence will be analyzed by using Mann- Whitley U test, Chi-square test, T-test or ANOVA.

**Analysis of intervention outcomes:** Consolidated standards of reporting trials (CONSORT standards) will be followed for reporting in this study [79]. For intervention arm and control arm comparison, indicators of rates of breast screening, breast self-examination and/or breast clinical exam at baseline, after three months and at the end of six months will be compared by using Chi-square and T-test. And logistic regression model will be used for predicting independent predictors of breast cancer screening behavior.

**Intention-to-treat (ITT):** Outcome will be analyzed under the basis of ITT. First, the principles of ITT will be applied to test the effects of attrition [80], which means that all participants who have been randomized will be included in the analysis. Missing endpoints will be imputed by using the Expectation- Maximization (EM) algorithm. To gauge the robustness of the outcomes, this analysis will be repeated while using Multiple-Imputation approach. Second, propensity score analysis will also be used. By using logistic model (1 for screening uptake and 0 for not) to predict the probability of be in breast screening behavior. And then use the predicted variable to replace the attrition of dummy variable.

Analysis of intervention mechanism in correlation analyses between each aspect of participants’ community based intervention adoption/use behaviors (e.g. frequency of breast screening by mammography, breast self-examination and/or clinical exam) and effectiveness of the intervention will be performed. A causal path model will be built according to correlation analyses results and related theories. And a path analysis will be subsequently conducted so as to calculate the residual path coefficient and determination coefficient, define causal relationships between different variables, and thus explore intervention mechanism of the community based intervention.

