**Perceived barrier of breast screening and Self-efficacy**

In a systematic review and meta-analysis conducted up to 2015 on the effectiveness interventions on breast screening in Asia and USA, health care workers into value their health. The perception of how confidentiality is handled influence women’s willingness to be screened [20, 21].

A study conducted in South Africa in uptake of screening among women after offering education shows uptake rate was increased [55, 56]. In another study, in the same country, the reasons for not screening were having already been screened for breast cancer, felt unready to be screen, the need to consult with partner, and refusing with no explanation [56-58]

In a cross sectional study conducted on attitude and perception on breast cancer screening in Ethiopia in 2011, experience among those who had been previously screened suffered from signs and symptoms, discrimination, and gap of healthcare worker confidentiality [59].

A study conducted on factors affecting cancer survival and screening among women in southern Ethiopia in 2014 shows women’s education, residing in urban, having open discussion about breast cancer screening with partners were statistically associated with screening uptake while among those who were not willing to be screened stigma and discrimination by the community were reasons for refusal of the screening [60].

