## 3.5. Sample Size and Sampling Technique

### 3.5.1. Sample size determination

For cluster level intervention, the sample size is calculated using double population proportion formula for cluster randomized trial [76, 77], with the assumption of the percentage of screening rate (π_0_) at the base line is similar in both groups; and Z_α/2_ the standard normal variable, at α = 5%; Z_β_ is (1-β) = 80%; **π_0_** is the prevalence of the participants who have knowledge about breast self-examination as screening methods since the affordable behavior is BSE (77.6%) [78]; a variable which gives maximum sample size; **π_1_** is the prevalence of screening rate in the intervention cluster/ kebele (87.6%) (Assumed to be increased by 10%); k is coefficient of variation of true proportions of the outcome variable between the clusters within each group. Since there is no study to estimate k, it is taken as 0.25.

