**Three districts (Two Woredas and one city administration in control arm (15 kebeles))**

**Three districts (Two districts and one city administration in intervention arm (15 kebeles))**

**405 samples for control arm from each district accordingly**

**405 samples for intervention arm from each district accordingly**

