### Randomization

Randomization will be carried out using a computer program by the investigators. The different kebeles will be alphabetically coded (A, B, C, D and so on) and participants attached to each kebele will be given numerical codes (for example, participants in kebele Y will be numbered Y001, Y002, Y003 and so on. Participants in the randomized controlled trial will be assigned 1:1 to the intervention and control arms under restricted randomized design after informed consent and collection of baseline data. The allocation sequence will be generated and released to the interventionist on a case-by-case basis by another independent department specializes in generating research random sequence. Interventionist, data collectors, statistician are not the same persons. Interventionists also acknowledge all those contacted are in the intervention arm. But anonymous responses will be entered into the database by a person unconnected with the project.

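### Section 3.9 compares the arms with individual-level tests that ignore both kebele clustering and the balance on district type; as written this inflates the type I error, and a clustered model without district type could be mildly conservative

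*Protocol*

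**What the plan says.** Section 3.9 (Data Analysis) fixes the arm comparison: rates "at baseline, after three months and at the end of six months will be compared by using Chi-square and T-test". The logistic regression mentioned next is for identifying predictors of screening behaviour. It is not described as multilevel, nor as the test of the arms.

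Other parts of the Protocol describe a different structure:

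- The Summary assigns a multilevel logistic regression to the quantitative analysis, to handle intra-cluster correlation.
- Section 3.5.1 multiplies the sample size by a design effect of 1.5 and separately states a between-cluster coefficient of variation k of 0.25.
- Figure 2 shows, for control, "Three districts (Two Woredas and one city administration in control arm (15 kebeles" and, for intervention, "Three districts (Two districts and one city administration in intervention arm (15 kebeles". Both city administrations of the Zone are in the sample, so each arm receives exactly one.
- The Data Quality Control section gives a reason for the district selection: spreading socioeconomic differences between districts.
- The Randomization section says participants are "assigned 1:1 to the intervention and control arms under restricted randomized design", without naming the restricting factor.
- Chapter Two reports a southern Ethiopian study in which "residing in urban, having open discussion about breast cancer screening with partners were statistically associated with screening uptake". The Protocol therefore has grounds to regard district type as prognostic.

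**The concern.** An analysis should reflect how units were allocated. Two features are missing from section 3.9, and they act in opposite directions.

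Ignoring clustering treats 405 women per arm as independent when they come from 15 kebeles. The standard error is too small and false positives rise.

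Ignoring a prognostic factor that was balanced by design leaves the city/woreda difference in the estimated between-kebele variance, although balance has removed it from the true variance of the effect. In an otherwise valid clustered analysis this makes the standard error too large and costs power.

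The first effect governs the test as written. The second matters for the natural repair, because the Summary's model is described only as a remedy for intra-cluster correlation and no district-type term is mentioned.

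**Working it through.** **The plan's figures.** 245 × 1.5 = 367.5, taken as 368; 368 + 36.8 = 404.8, taken as 405 per arm. The 245 matches the continuity-corrected two-proportion formula; the printed line gives 218. Nothing below depends on that. Women per kebele: 810 / 30 = 27.

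**Error of the Chi-square at the plan's design effect.** The implied ICC is 0.5 / 26 = 0.019. The standard error is too small by √1.5 = 1.22. Actual error = 2[1 − Φ(1.96 / 1.22)] = 11.0%.

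**At the stated k = 0.25.** ICC = 0.25² × 0.776 / 0.224 = 0.217; design effect = 1 + 26 × 0.217 = 6.6; actual error about 45%.

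**Adding the balance on district type.** The documents give neither the city/woreda gap nor the kebele split. Assume 5 of each arm's 15 kebeles are in the city administration, a 10-point gap, and a total ICC of 0.0204 that includes the gap.

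- Individual variance: 0.776 × 0.224 = 0.1738.
- Between-kebele variance: 0.0204 × 0.1738 = 0.00355.
- Part due to district type: (1/3)(2/3)(0.10²) = 0.00222, or 63% of it.
- Variance of a kebele proportion: 0.00355 + (0.1738 − 0.00355) / 27 = 0.00985. With district type removed: 0.00985 − 0.00222 = 0.00763.
- Chi-square: true / assumed variance = (0.00763 / 15) / (0.1738 / 405) = 1.185. Error = 2[1 − Φ(1.96 / √1.185)] = about 7%.
- Kebele-level t-test without district type (28 df): true / estimated standard error = √(0.00763 / 0.00985) = 0.88. Error = P(|t| > 2.048 / 0.88) = about 2.7%.

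**Simulation.** 20,000 trials per setting, 77.6% v 87.6% for power, same assumptions. A kebele-level test stands in for the multilevel model. Repeat runs differ by up to about a point.

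| Assumed gap | Chi-square error | Kebele-level error, without v with district type | Power, without v with |
|---|---|---|---|
| 5 points | 10.5% | not tabulated | 82% v 84% |
| 8 points | 8.7% | 3.3% v 4.8% | 83% v 87% |
| 10 points | 7.0% | 2.4% v 4.8% | 83% v 90% |
| 12 points | 5.3% | 1.7% v 4.8% | 85% v 95% |

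**Sensitivity.**

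- If the gap is added on top of an ICC of 0.019 instead of forming part of the total, the Chi-square error falls only from 11.0% to 10.7%, 10.0% and 8.9% at gaps of 10, 20 and 30 points.
- At k = 0.25 a 10-point gap is 0.00222 / (0.217 × 0.1738) = 6% of the between-kebele variance, and power is about 22% v 24%.
- If whole districts are allocated and an assumed district-level ICC of 0.005 lies within the 0.0204, the kebele-level test has 8.5%, 7.6% and 6.5% error at gaps of 5, 8 and 10 points. Adding district type gives 9.7%, 10.2% and 10.7%.

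**The case against.** A reader might infer from Figure 2 that the planned tests, by ignoring the balance, give error bars that are too wide and throw power away. The documents do not support that. The Chi-square ignores clustering as well, and in every setting above its error stays over 5%. Balance would outweigh clustering only at an ICC below about 0.0005, 0.002 or 0.005 for gaps of 10, 20 or 30 points, against 0.019 implied by the design effect. Stratifying the Chi-square by district type alone would narrow its error bars further. Conservatism arises only in a cluster-valid analysis that omits the factor.

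Other objections carry weight:

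- **Size.** The gap is assumed; the Protocol cites only an association. Within a total ICC of 0.0204 the 12-point case takes 90% of the between-kebele variance and leaves a residual ICC of about 0.002, which is extreme.
- **Restriction.** No passage names district type as a stratification factor. It is read from Figure 2, supported by the Data Quality Control section.
- **Unit.** The conservative result presumes kebeles are allocated within district type. Figure 2 and the Data Quality Control section can be read as allocating whole districts, in which case a kebele-only model with district type is itself anti-conservative.
- **Scope.** Covariates are commonly left to the SAP, so the missing district term alone would not be a fault, and omitting it does not bias the comparison. But section 3.9 goes further: it names tests that contradict the Summary and the sample size. A T-test on kebele proportions would respect clustering, but the section does not say that is meant.

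**Conclusion.** The concern holds in this form. Section 3.9 specifies an arm comparison that respects neither feature of the allocation, and its net fault is anti-conservative: about 11% type I error at the plan's own design effect, about 7% if a 10-point gap accounts for part of the clustering, and about 45% at the stated k.

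The district-type term is a secondary point. Once clustering is handled, and if kebeles are the allocated unit, including it restores the nominal error rate and gains about 7 points of power at an assumed 10-point gap and ICC of 0.02. The gain is about 2 points at a 5-point gap or at k = 0.25. These figures rest on an assumed gap, one third of kebeles in cities, and equal kebele sizes of 27. If whole districts are allocated they do not apply, and allowing for kebeles alone is not enough.

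**What to change.** In section 3.9, replace the Chi-square and T-test as the primary arm comparison with the multilevel logistic model already named in the Summary. Include a random effect for the unit actually allocated and a fixed effect for district type (city administration v woreda). State that any factor used to restrict the allocation enters the primary model.

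Reconcile the Sampling techniques section (30 kebeles divided between arms), Figure 2 and the Data Quality Control section (districts placed in arms), and the Randomization section (participants assigned) on what is allocated. If it is the district, the model needs a district-level random effect as well as kebele.

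**Cost.** A sentence or two of text and no new data, since district type is known for every kebele. With kebeles allocated, the extra term takes one of 28 degrees of freedom (30 − 2), for a gain that may be small. With districts allocated the price is much higher: six districts leave 6 − 2 = 4 degrees of freedom, or 3 with district type. The unit should therefore be settled before the model is fixed.

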**Control group (n=405)**

- Usual care (services)
- Welcome message
- No continuous follow up

Phase 2 follow up assessment at the end of 3^rd^ and 6^th^ month

**Main outcome:** Screening Uptake **Secondary outcomes:** Increased knowledge, attitude and intention to screening

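### The planned attrition analyses (EM, multiple imputation, propensity score), as ordinarily used, all assume data missing at random, so none can show whether the result withstands outcome-dependent loss

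*Protocol*

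**What the plan says.** The intention-to-treat paragraph of protocol section 3.9 (Data Analysis) sets the purpose: "First, the principles of ITT will be applied to test the effects of attrition". It defines the analysis set: "all participants who have been randomized will be included in the analysis". It then names three analyses.

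- Main handling: "Missing endpoints will be imputed by using the Expectation- Maximization (EM) algorithm".
- Check on it: "To gauge the robustness of the outcomes, this analysis will be repeated while using Multiple-Imputation approach".
- Further analysis: "Second, propensity score analysis will also be used". This is a logistic model for screening uptake, followed by "And then use the predicted variable to replace the attrition of dummy variable".

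The paragraph names no missing-data mechanism, and none of its analyses lets lost women differ from seen women beyond what the recorded data explain.

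Contact differs between arms. Under 3.7.2.2, intervention women have sessions every 15 days for three months and leave phone numbers for tracking and reminders. Fig. 3 adds continuous follow-up for them, while the control box reads "No continuous follow up". Outcome visits are the same in both arms: baseline, three months and six months (3.7.2.4).

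**The concern.** A check on attrition has to vary the assumption that attrition may break. Here that assumption is that, given the recorded data, women who are not seen at three or six months screen as often as women who are. Moving from EM to multiple imputation changes the algorithm and keeps the assumption. If the two use the same imputation model they target the same quantity, so their point estimates stay close whether or not that quantity is biased.

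The propensity-score step does not fill the gap. Its wording leaves open whether it models uptake or drop-out, but either way the model is fitted to observed data.

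This matters because the outcome comes from repeat questionnaires on a behaviour. Interest in screening may well affect both the behaviour and continued attendance, and the arms differ in how closely women are followed. Close agreement between EM and multiple imputation could then be taken as reassurance about attrition that it does not give.

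**Working it through.** **Inputs from the protocol (3.5.1).** Control rate 77.6%, intervention rate 87.6%, design effect 1.5, 405 women per arm, 10% allowance for non-response or recording error. The last steps of the sample size reproduce: 245 × 1.5 = 367.5, rounded to 368; 368 × 1.10 = 404.8, rounded to 405. The protocol gives no figure for expected loss to follow-up, so 10% missing is used below as an assumption, with 5% and 20% as a range.

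**1. Size and direction of the bias under outcome-dependent loss.** Let the true rate be p, the share lost m, and the lost women's uptake g below p. The rate among seen women is then p + g·m/(1 − m). Without informative covariates, this is what both EM and multiple imputation return. With no true effect (p = 0.776 in both arms) and g = 0.30:

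- Intervention, 5% lost: 0.776 + 0.30 × 0.05/0.95 = 0.792
- Control, 15% lost: 0.776 + 0.30 × 0.15/0.85 = 0.829
- Difference: about -3.7 points. With the loss rates reversed: about +3.7.

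With g = 0.50 the figures are 0.802 and 0.864, or about -6.2 points (+6.2 reversed). If the true effect is 10 points, the 30-point gap gives about 10 − 3.7 = 6.3 with 5% intervention and 15% control loss, and about 13.7 with the reverse.

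**2. Do EM and multiple imputation diverge as the bias grows?** A simulation used 2,000 trials per row, 405 women per arm, a true difference of about 10 points, one binary covariate in both imputation models, about 10% missing per arm and variance × 1.5. EM-filled data were analysed as complete; multiple imputation used 20 imputations and Rubin's rules. Control loss was 10% regardless of outcome. Intervention loss depended increasingly on the outcome.

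| Intervention loss, unscreened / screened | EM (points) | MI (points) | Mean absolute gap (points) | Significance verdict differs |
|---|---|---|---|---|
| 10% / 10% (missing at random) | 9.98 | 9.98 | 0.15 | 2.2% |
| 30% / 7.16% | 12.64 | 12.64 | 0.15 | 0.4% |
| 50% / 4.34% | 15.43 | 15.42 | 0.15 | 0.0% |
| 80% / 0.1% | 19.55 | 19.55 | 0.13 | 0.0% |

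In the last row the bias is 19.55 − 9.96 = 9.6 points, about the size of the planned effect, and the two methods still agree.

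**3. What the multiple-imputation repeat does test.** The standard error is √{1.5 × [0.876 × 0.124 + 0.776 × 0.224]/n}. With n = 405 (filled data treated as complete) it is 0.0323. With n = 405 × 0.9 = 364.5 (approximating multiple imputation) it is 0.0341. The ratio is 1.05 at 10% missing, 1.03 at 5% and 1.12 at 20%. The repeat can therefore turn a borderline result non-significant, but through variance, not through bias.

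**4. What varying the assumption shows.** Take the observed rates as 87.6% and 77.6%, with a share m missing in each arm. Let q₁ and q₀ be the uptake of lost intervention and lost control women. The difference is [(1 − m) × 0.876 + m·q₁] − [(1 − m) × 0.776 + m·q₀].

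| Lost women | 5% missing | 10% missing | 20% missing |
|---|---|---|---|
| As observed (EM, MI) | +10.0 | +10.0 | +10.0 |
| Intervention at half the observed rate (q₁ = 0.438), controls as observed | +7.8 | +5.6 | +1.2 |
| Intervention none screened (q₁ = 0), controls as observed | +5.6 | +1.2 | -7.5 |
| None screened in either arm | +9.5 | +9.0 | +8.0 |

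For example, at 10% missing: 0.9 × 0.876 + 0.1 × 0.438 = 0.8322, and 0.8322 − 0.776 = 0.0562.

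**The case against.** Several stronger readings are tempting, and the protocol does not support them.

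- *A reader might infer that EM against multiple imputation is the only check.* It is not: 3.9 also lists the propensity-score analysis. That analysis shares the blind spot, but it is there.
- *A reader might infer that agreement between the two is a rule for declaring the result robust.* The protocol states no agreement rule and no threshold; it says only that robustness will be gauged.
- *A reader might infer that the repeat can never weaken the result.* It can, through imputation variance, as step 3 shows.
- *A reader might infer that attrition will create a false benefit.* The direction is open. Thinner follow-up of controls points to more loss there, and if lost women screen less, that biases against the intervention.

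There are further fair points. The simulated agreement follows almost by construction once both methods share an imputation model, and the protocol does not state that model. Baseline perceptions, past screening behaviour and three-month data could all enter the imputation and reduce the bias. Women who cannot stay through the intervention period are excluded, and both arms have the same outcome visits. Sensitivity analyses are often left to a statistical analysis plan, which is not at hand.

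These points limit the likely size of the bias and the wording of the finding. They do not remove it. Better predictors shrink the bias but cannot reveal what remains. The finding also does not rest on missing detail: the protocol names a specific method for a specific purpose, and that method does not serve it.

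**Conclusion.** The point holds in this limited form: the attrition analyses in 3.9 cover imputation uncertainty but not outcome-dependent attrition, so the stated aim is not met. It rests on EM, multiple imputation and the propensity model being used in their ordinary missing-at-random form, with nothing in the protocol departing from that. Such loss is plausible, given the unequal contact between arms, but not established. The protocol supplies only a 10% contingency; every loss rate and uptake gap above is an assumption. Under those assumptions the undetected bias is a few points in either direction, against a planned effect of 10 points, and it approaches 10 points only in the most extreme pattern simulated. This should be changed before analysis.

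**What to change.** In 3.9, keep multiple imputation, because it carries the imputation variance, but stop using its comparison with EM as the gauge of robustness to attrition. Put a pre-specified delta-adjusted (tipping-point) multiple-imputation analysis in that role:

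- lower the imputed uptake of missing women in fixed steps (for example 0, 10, 20, 30 and 50 points), separately by arm;
- include the extreme in which missing intervention women count as not screened while missing controls keep their imputed values;
- report the shift at which the conclusion changes.

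As an illustration with +10 points observed, 10% missing per arm and the standard error held at 0.0341, significance is lost once the difference falls below 1.96 × 0.0341 = 6.7 points. That is a shift of (10 − 6.7)/0.10, or about 33 points, in lost intervention women alone. The standard error would itself change somewhat with the shift, so this is approximate.

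The cost is a short change of wording and a few extra runs of an imputation already planned, with no new data. The downside is that the result may have to be reported as less robust.

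### The intention-to-treat analysis rests on EM fill-in with no stated variance correction, and the propensity model meant to address attrition predicts screening uptake instead of loss to follow-up

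*Protocol*

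**What the plan says.** Everything on this point stands in the Data Analysis section of the protocol (3.9).

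- **Analysis set:** "all participants who have been randomized will be included in the analysis".
- **First-line handling:** "Missing endpoints will be imputed by using the Expectation- Maximization (EM) algorithm". The section does not say how the uncertainty of these values reaches the test, or whether study arm is in the imputation model.
- **Robustness repeat:** "To gauge the robustness of the outcomes, this analysis will be repeated while using Multiple-Imputation approach".
- **Test between arms:** screening rates "will be compared by using Chi-square and T-test". The Summary names a multilevel logistic regression model instead.
- **Second approach to attrition:** a propensity score analysis, described as "By using logistic model (1 for screening uptake and 0 for not) to predict the probability of be in breast screening behavior". The result is then used as follows: "And then use the predicted variable to replace the attrition of dummy variable".

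The only figure that could stand in for missingness is the 10% added in Sample size determination (3.5.1). It is labelled as covering non-response or recording error, not loss to follow-up.

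**The concern.** Two separate things are at stake.

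**The primary p-value.** EM gives sound parameter estimates, but a data set completed once by EM and then passed to a chi-square test or t-test treats imputed values as observed. Multiple imputation carries the missing uncertainty into the standard error, yet here it is only the check. The method without a stated correction supplies the main result.

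**The attrition check.** A propensity model for attrition has being lost (1) or observed (0) as its dependent variable. The model described has screening uptake as its dependent variable, so it is an outcome regression. Reporting it as evidence that attrition does no harm would mislead.

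Attrition deserves care in this trial because contact differs by arm. The participant flow chart (Fig. 3) gives continuous follow-up to the intervention arm and none to the control arm, and section 3.7.2.2 adds phone tracking and reminders for intervention participants. Unequal loss is plausible, and that is the situation an attrition model should examine.

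**Working it through.** **Inputs from the protocol (3.5.1).** Two-sided alpha 5%, rates 77.6% and 87.6%, and 405 women per arm. The last steps to 405 reproduce: 245 × 1.5 = 367.5, rounded to 368; 368 × 1.10 = 404.8, rounded to 405. The protocol gives no figure for the effect of missing data, so there is none to reproduce.

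**Assumptions.** A fraction d of outcomes is missing completely at random and women are independent. Clustering is left out because it is a separate issue. I take d = 10% as the central scenario and show 5-30%.

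**Case A: arm-specific fill, analysed as observed.**

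*Predicted mean filled in (t-test).* The naive variance per arm is about (1−d)·p(1−p)/n. The correct variance is p(1−p)/[n(1−d)]. The naive SE is therefore (1−d) times the correct one, and

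type I error = 2·[1 − Φ(1.96·(1−d))].

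- d = 10%: 2·[1 − Φ(1.764)] = 0.078
- d = 20%: 2·[1 − Φ(1.568)] = 0.117
- d = 30%: 2·[1 − Φ(1.372)] = 0.170

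*One random draw filled in (chi-square possible).* The true variance is p(1−p)/n × [1/(1−d) + d], against a naive p(1−p)/n, so

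type I error = 2·[1 − Φ(1.96/√(1/(1−d) + d))].

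- d = 10%: 1.111 + 0.1 = 1.211; 1.96/√1.211 = 1.781; 0.075
- d = 20%: 1.25 + 0.2 = 1.45; 1.96/√1.45 = 1.628; 0.104
- d = 30%: 1.429 + 0.3 = 1.729; 1.96/√1.729 = 1.491; 0.136

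Simulation with 405 per arm and a true rate of 0.776 in both arms (200,000 trials; 20,000 for multiple imputation) agrees:

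| Missing | Mean fill by arm | One draw by arm | Mean fill, no arm in model | Most likely value (1) filled | Multiple imputation, arm in model |
|---|---|---|---|---|---|
| 5% | 0.063 | 0.062 | 0.051 | 0.049 | 0.052 |
| 10% | 0.078 | 0.074 | 0.050 | 0.047 | 0.052 |
| 20% | 0.118 | 0.105 | 0.050 | 0.044 | 0.053 |
| 30% | 0.171 | 0.136 | 0.051 | 0.041 | 0.051 |

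At d = 10% with mean fill, a correct p of 0.05 is reported as 2·[1 − Φ(1.96/0.90)] = 0.029.

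*With a useful predictor.* The same data are collected at 3 and 6 months, so the 3-month outcome can inform the fill. With arm-specific mean fill and an assumed 3- to 6-month correlation of 0.5, a simulation gives type I error of about 0.068, 0.097 and 0.133 at 10%, 20% and 30% missing. At a correlation of 0.7 it gives 0.066, 0.080 and 0.102 (40,000 trials each).

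**Case B: arm omitted from the model.** The fill is the pooled rate, (77.6 + 87.6)/2 = 82.6%. At d = 10%:

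- Control: 0.9 × 77.6 + 0.1 × 82.6 = 78.1%
- Intervention: 0.9 × 87.6 + 0.1 × 82.6 = 87.1%
- Difference: 9.0 points instead of 10

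**Case C: most likely value (1) filled in.** At d = 10%:

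- Control: 0.9 × 77.6 + 10 = 79.84%
- Intervention: 0.9 × 87.6 + 10 = 88.84%
- Difference: 9.0 points, with uptake overstated in both arms

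In B and C the difference is multiplied by (1−d), so it is 8 points at 20% missing.

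**The propensity step.** The phrase "use the predicted variable to replace the attrition of dummy variable" has two readings.

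- If predicted uptake fills the outcomes of lost women, the step is deterministic single imputation again, as in Case A or B.
- If it replaces an attrition indicator, predicted uptake sits where the probability of loss belongs.

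Under neither reading does the model contain information on who was lost.

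**The case against.** The strongest reply has four parts.

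1. **Multiple imputation is planned.** This stands. With arm in the model it holds type I error at 0.051-0.053, and a large gap from the EM result would show. It does not remove the defect, because the main result is still the EM one and the protocol gives no rule for the case where the two disagree.

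2. **The direction of the error is not fixed by the text.** This also stands. A reader might infer that the reported p-values will certainly be too small. The protocol does not support that: it leaves open whether arm enters the model and whether values are predicted, drawn or rounded. Cases B and C do not inflate type I error. They bias the effect towards zero instead, so they are no defence of the method.

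3. **The figures are near the upper end.** Partly right. Useful predictors reduce the inflation, as shown above. Fractional fills cannot enter a chi-square test, so the mean-fill column applies to the t-test only. The 10% is not an attrition rate, and the 20% and 30% scenarios have no source in the protocol. Women who cannot stay until the intervention is completed are also excluded at entry.

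4. **The propensity wording is unclear, and a statistical analysis plan may settle details.** The unclear wording means one cannot assert that outcomes will be replaced by predictions. The dependent variable, however, is stated explicitly and is the wrong one under either reading. That is an error in the text, not a detail left for later.

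**Conclusion.** The point holds in two parts.

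**EM as first-line handling.** With no variance correction stated, single fill-in either understates the standard error or biases the effect, and the protocol does not determine which. In the first case, two-sided type I error is up to about 7.4-7.8% at 10% missing and 10.5-12% at 20%, and lower when the 3-month outcome is predictive. In the second, type I error stays at or below about 5% and the arm difference shrinks by about the missing fraction. These sizes assume random loss and independent women, and the missing rates are assumptions. The harm is modest at 10% and serious at 20-30%. It would be wrong to conclude that p-values are necessarily too small, or that the protocol has no valid handling of missing data at all.

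**The propensity analysis.** It is mis-specified as written and cannot test or correct for attrition at any rate of loss. This part depends on no numerical assumption.

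The protocol should be changed on both parts.

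**What to change.** 1. Choose one primary analysis and drop EM single fill-in from that role. Either:
   - multiple imputation with arm, kebele, and baseline and 3-month behaviour in the imputation model, combined by Rubin's rules; or
   - the multilevel logistic model already named in the Summary, fitted to all observed outcomes.
2. Redefine the propensity model with loss to follow-up (1/0) as the dependent variable and arm and baseline variables as predictors. Use it for inverse-probability weights in a sensitivity analysis. Otherwise delete it.

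The main components are already named in the protocol. The cost is a change of wording, modest analysis work and slightly wider confidence intervals.
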